**SECTION 5 – POTENTIAL RISKS AND BENEFITS**

**5.1 POTENTIAL RISKS**

**5.1.1 General Risks of Study Protocol and Procedures**

The potential subject risks specifically related to the study protocol procedures could include:

Venipuncture:

The majority of subjects in this investigation will have existing access for obtaining blood specimen so no venipuncture will be required. For the unlikely subject without vascular access, the risks of the venipuncture are mild and include temporary, minor discomfort which is likely (>25% of the time), bruising which is likely, and which may last for several days, and rarely (<1% of the time) infection, bleeding and phlebitis.

Loss of confidentiality:

The risk of loss of confidentiality with respect to data is rare.

**5.1.2 Potential Risks of Experimental Intervention**

Insertion of a central venous catheter for plasmapheresis:

Complications of this procedure include bleeding at the insertion site, pneumothorax, catheter-associated blood clots and infections (local and systemic). The complication rate of central vein catheters, inserted by physicians of variable experience, has been reported to be 15%.80

Plasmapheresis: The most common adverse effect is a drop in blood pressure associated with symptoms of dizziness or light-headedness79. Unusual complications include extracorporeal coagulation. The addition of citrate to the infusion solutions can lead to hypocalcemia with associated peri-oral tingling, numbness and more rarely muscle irritability, cardiac arrhythmias, and seizures.

Rare complications are infections by blood products (fresh frozen plasma (FFP)), transfusion reaction to FFP, an allergic reaction to the replacement solutions or sterilizing agents for the tubing, and adverse effects of immunosuppression produced by the associated hypogammaglobulinemia. Medications dosing may also need to be adjusted in patients being treated with plasmapheresis as certain medications can be removed by the procedure.

Rituximab:

The most common adverse effects (>10%) with rituximab from available clinical trials include74,78:

General: Fever (5% to 53%), chills (3% to 33%), headache (19%), pain (12%)

Dermatologic: Rash (1-15%), pruritus (5% to 14%), angioedema (1-11%)

Gastrointestinal: Nausea (8% to 23%), abdominal pain (2% to 14%)

Hematologic: Cytopenias (2-49%)

Neuromuscular & skeletal: Weakness (2% to 26%)

Respiratory: Cough (13%), rhinitis (3% to 12%)

Infusion Related: angioedema, bronchospasm, chills, dizziness, fever, headache, hyper-/hypotension, myalgia, nausea, pruritus, rash, rigors, urticaria, and vomiting; reactions (7-39%)

Less common adverse reactions (1% to 10%) include:

Cardiovascular: Hypotension (2-10%), peripheral edema (8%), hypertension (6% to 8%), flushing (5%), edema (<5%)

Central nervous system: Dizziness (10%), anxiety (2% to 5%), agitation (<5%), depression (<5%), hypoesthesia (<5%), insomnia (<5%), malaise (<5%), nervousness (<5%), neuritis (<5%), somnolence (<5%), vertigo (<5%), migraine (RA: 2%)

Dermatologic: Urticaria (2% to 8%)

Endocrine & metabolic: Hyperglycemia (9%), hypoglycemia (<5%), hypercholesterolemia (2%)

Gastrointestinal: Diarrhea (10%), vomiting (10%), dyspepsia (3%), anorexia (<5%), weight loss (<5%)

Hematologic: Anemia (3-8%)

Local: Pain at the injection site (<5%)

Neuromuscular & skeletal: Back pain (10%), myalgia (10%), arthralgia (6% to 10%), paresthesia (2%), arthritis (<5%), hyperkinesia (<5%), hypertonia (<5%), neuropathy (<5%)

Ocular: Conjunctivitis (<5%), lacrimation disorder (<5%)

Respiratory: Throat irritation (2% to 9%), bronchospasm (8%), dyspnea (7%), upper respiratory tract infection (RA: 7%), sinusitis (6%)

Miscellaneous: LDH increased (7%)

Rare events associated with rituximab include severe mucocutaneous reactions, progressive multifocal leukoencephalopathy due to LC virus reactivation, hepatitis B reactivations, and other infections.78

**5.2 ALTERNATIVE TREATMENTS**

The alternative treatments for the subjects participating in this investigation are to continue their medical care under the direction of their attending physician.

**5.3 POTENTIAL BENEFITS**

Participation in the proposed research will not provide a direct benefit to participants in this research. Information obtained from the proposed research will provide information about the relationship between IPF treatment and patient outcome. Potential benefits from the participation in these protocols include enhanced survival, improved respiratory symptoms, and decreased exacerbation severity. Identification of the mechanism(s) mediating these outcomes will facilitate risk-stratification for these adverse outcomes, and development of targeted treatment strategies for the future.

The alternative treatments for the subjects participating in this investigation are to continue their IPF care under the direction of their primary physician.

Based on the preceding assessment of risks and potential benefits, the risks to subjects are reasonable in relation to anticipated benefits. The research presents a balance of risks and expected direct benefits similar to that available in the clinical setting.

Importance of the Knowledge to be Gained

The preliminary data in this application outline a hypothesis for the progressive clinical deterioration in patients with advanced IPF and disease exacerbations. The protocol specifically seeks to address that hypothesis. If the study intervention is found to be both safe and effective in the study population, the treatment of IPF would be altered significantly, and ultimately could lead to a change in the disease natural history. Completion of these protocols will begin to address important questions related to disease.

**5.4 DATA SAFETY MONITORING PLAN**

**5.4.1 Data Safety Monitoring Board**

The local Data Safety Monitoring Board (DSMB) chaired by [name], the PI of this clinical trial, is comprised of members including senior experts in pulmonary medicine, clinical research, and clinical trial design, biostatistics, and research ethics. The DSMB will conduct interim monitoring of accumulating data from research activities to assure the continue safety of human subjects, relevance and appropriateness of the study, and the integrity of research data.

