- A summary of cumulative data related to unanticipated problems (including adverse events) including a determination of causality and whether the risk to benefit assessment has changed.
- If appropriate, a summary of pertinent scientific literature reports, therapeutic developments, or results of related studies that may have an impact on the safety of study participants or the ethics of the research study.
- A summary of the outcome of reviews conducted to ensure subject privacy and research data confidentiality.
- Final conclusions regarding changes to the anticipated benefit-to-risk assessment of the study participation and final recommendations related to continuing, changing, or terminating the study.

Stopping Rule:

For safety reasons, we propose to discontinue this combined treatment if first 2 of the 10 subjects enrolled in the study experience any unexpected fatal or life-threatening events that can be attributed to the study drug, the study will be halted, until data review by investigators and the Data Safety Monitoring Board has rendered a final recommendation about study continuation.

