**5.4.3 Parameters to be Monitored**

The following progress will be monitored throughout the course of the research to ensure the safety of subjects as well as the integrity and confidentiality of their data.

- An evaluation of the progress of the research study, including subject recruitment and retention, and an assessment of the timeliness and quality of the data.
- A review of collected data (including adverse events, unanticipated problems, and subject withdrawals) to determine whether there is a change to the anticipated benefit-to-risk assessment of study participation and whether the study should continue as originally designed, should be changed, or should be terminated.
- An assessment of external factors or relevant information (eg. Pertinent scientific literature reports or therapeutic development, results of related studies) that may have an impact on the safety and study participants or the ethics of the research study.
- A review of study procedures designed to protect the privacy of the research subjects and the confidentiality of their research data.

The National Cancer Institute Common Toxicity Criteria Scale (Appendix 3) will be used to define grades (severity) of adverse events and toxicities. Previous experience with rituximab has demonstrated common side effects that may occur during treatment. An adverse event is any untoward medical occurrence in a participant who received study drug, regardless of its relationship to the study drug. Toxicity is an adverse event with a direct relationship to the study drug. All toxicities are adverse events, but not all adverse events are toxicities. This is a determination made by the study investigator. The study investigators will classify adverse events as “definitely or most likely,” “possibly,” or “very unlikely” due to the study drug. Toxicity will be defined as an adverse event that is definitely, most likely, or possibly caused by the study drug.

The severity of adverse changes in physical signs or symptoms will be classified as follows:

- Grade 1 (Mild): asymptomatic or mild symptoms; clinical or diagnostic observation only; intervention not indicated.
- Grade 2 (Moderate): minimal, local or noninvasive intervention indicated; limiting age-appreciate instrumental ADL (Activities of Daily Living).
- Grade 3 (Severe): medically significant but not immediately life-threatening; hospitalization or prolongation of hospitalization indicated; disabling; limiting self care ADL.

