**5.4.4 Frequency of Monitoring**

The principal investigator will review subject safety data as it generated. The principal investigator, co-principle investigators, and the research staff will meet on a two week interval to re-evaluate study goals, subject recruitment, data coding and retention, documentation and identification of adverse events, complaints and confidentiality of subjects. There will be an evaluation of the progress of the research study, including assessments of data quality, time lines, participant recruitment, accrual, and retention. The principal investigator will also review the outcome and adverse event data to determine whether there is any change to the anticipated benefit-to-risk ratio of study participation and whether the study should continue as originally designed or should it be re-evaluated and changed.

The DSMB will also be expected to meet as needed, but not less than, every six months to provide an overall summary status report to the regulatory agencies.

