**5.5.2 Protection Against Potential Risks of Experimental Intervention**

Despite the documented safety profile of rituximab and plasmapheresis in other human disorders of abnormal immune regulation, the study has been designed with a focus on protecting patients against risk including:

Selection of a target patient population with a very high risk of morbidity and mortality due to the absence of a defined treatment for the disorder

Involvement of trained staff in central venous access placement for the provision of plasmapheresis and utilization of ultrasound guidance for placement of all catheters

Involvement of trained hospital staff for the provision of plasmapheresis in patients with advanced medical illness

Involvement by trained staff / investigators with experience in the administration of Rituximab

Prior human experience with the study medication in similar conditions with an autoimmune hypothesis including rheumatoid arthritis and myositis

Exclusion of all patients with conditions which might simulate IPF exacerbations such as congestive heart failure, pneumonia, and pulmonary thromboembolism

Continuous monitoring by an independent Data and Safety Monitoring Board

Rituximab:

The patient population will receive pre-treatment with acetaminophen (650mg), diphenhydramine (50mg), and methylpredisolone (100mg IV) prior to drug administration. Based upon the experience of the study investigators to date, this regimen will significantly lessen the risk of general reactions to the medication including fever (5% to 53%), chills (3% to 33%), headache (19%), and pain (12%).

Plasmapheresis: The subject will undergo routine monitoring of coagulation parameters (INR) with correction of acquired defects during the procedure consistent with existing medical practice.

Required Education in the Protection of Human Research Participants

All principal and co-investigators listed on University of Pittsburgh Institutional Review Board approved protocol are required to participate in a course entitled The Education and Certification Program in Research & Practice Fundamentals (RPF). This web based tutorial is a requirement of the IRB for protocol submission.

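### Protocol 5.5.2 promises an independent DSMB, but 5.4.1 makes the trial's own PI its chair; the conflict matters most for the recommendation to continue after a safety halt

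*Protocol*

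**What the plan says.** Section 5.4.1 of the Protocol opens by identifying the chair of the local board and then its members: "the PI of this clinical trial, is comprised of members including senior experts in pulmonary medicine". Other fields on the list include biostatistics, trial design and research ethics. It does not say whether any member is outside the study team.

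Section 5.5.2 lists the design features meant to protect subjects from the risks of rituximab and plasma exchange. One of them is "Continuous monitoring by an independent Data and Safety Monitoring Board".

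The stopping rule in 5.4.2, which concerns events put down to the drug, applies "if first 2 of the 10 subjects enrolled in the study experience any unexpected fatal or life-threatening events that can be attributed to the study". Where that condition is met, the rule provides that "the study will be halted, until data review by investigators and the Data Safety Monitoring Board has rendered a final recommendation about study continuation". Section 5.4.2 also gives the PI primary responsibility for overseeing data and safety monitoring, and has the PI work with the reporting investigators on the written event summaries that go to the DSMB and the IRB.

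On whether an adverse event is drug-related, 5.4.3 says: "This is a determination made by the study investigator". Section 5.4.4 has the board meet as needed, with a floor of "not less than, every six months".

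**The concern.** Independence is a factual property of a board, and the Protocol both asserts it and describes a board that lacks it. The removal of the chair's name does not create the problem, because the text that remains identifies the chair by role. Nor is this a detail that could wait for a statistical analysis plan: the Protocol itself fixes the board's composition and makes the claim.

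The stake is how far the safety conclusions can be trusted. Safety is a primary outcome (2.3.1), the trial is open-label, the survival comparison is with historical controls, and the investigators state that they expect high efficacy (2.4.1). In these patients many deaths could be put down either to the disease or to the treatment, and the halting rule turns on that judgement. A reader of 5.5.2, such as an ethics committee, would take it that people outside the study team review that judgement.

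**Working it through.** There is no design calculation to reproduce. The check is to follow a serious event through the Protocol and note who acts at each step.

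1. **Attribution.** Under 5.4.3 the study investigators classify relatedness. The stopping rule does not say in terms that it uses this classification, but no other attribution process is described.
2. **Trigger.** Under 5.4.2 the halt needs unexpected fatal or life-threatening events attributable to study drug in the first 2 of the 10 subjects. It therefore depends on step 1.
3. **Evidence.** Under 5.4.2 the PI and the reporting investigators prepare the summary sent to the board.
4. **Continuation.** The halt lasts "until data review by investigators and the Data Safety Monitoring Board has rendered a final recommendation about study continuation". Two parties are named: the investigators, and a board whose chair is the PI under 5.4.1. The IRB is not named here.

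At none of these four steps does the Protocol name a party that it shows to be outside the study team. Other board members may be outside it, but 5.4.1 does not say so.

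**How often attribution could be needed.** Section 1.3 gives a hospital mortality of about 50% for IPF exacerbations. If trial subjects died at that rate (an assumption, for scale only), the expected number of deaths is 10 × 0.50 = 5. Judgements on whether a death was unexpected and drug-related would then be routine.

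**What reaches the IRB.** Under 5.4.6, unexpected fatal or life-threatening events associated with study drug or procedures go to the DSMB and the IRB within 24 hours; other serious unexpected associated events go within 5 working days. Under 5.4.2 the IRB also receives the written summaries, and a DSMB report at continuing review, annually or more often, with a causality determination and a recommendation on continuing, changing or terminating. However, 5.4.5 defines a serious adverse event as one the investigator thinks study-related, so step 1 also filters the expedited reports. The causality determination at continuing review is part of the report from the PI-chaired board.

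**Meeting frequency.** Section 3.1 expects enrolment within one calendar year. The six-month floor gives 12 ÷ 6 = 2 guaranteed meetings in that time. This is a minimum, since 5.4.4 also provides for meetings as needed.

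**The case against.** The strongest reply is that the trial has outside oversight and that the conflict is one of wording. Several stronger inferences that a reader might draw do fail on the text.

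- *That the board is the only check on investigator attribution.* It is not. The IRB receives 24-hour and 5-working-day reports, written summaries and the board's reports. It is a partial check, limited because the expedited reports pass through investigator attribution and the restart rule does not mention it.
- *That all 10 subjects could be treated with only two board reviews even if safety events occurred.* Two is the floor when nothing prompts a further meeting. The board meets as needed, receives urgent reports within 24 hours, and must review the data after a halt.
- *That there is in effect no board, or that the PI controls its decision.* The membership list includes other experts, no voting or quorum rule is given, and the board issues a recommendation. What is shown is impaired independence.

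These points narrow the concern without removing it. Expertise is not independence, and a board with other qualified members is still not independent when the trial's PI chairs it. If the chair's description in 5.4.1 is a drafting slip, that section still needs correcting.

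**Conclusion.** The contradiction between 5.4.1 and 5.5.2 stands on the Protocol's own words and must be resolved. Its practical weight falls on the continuation recommendation in 5.4.2, because the investigators supply the attribution, the PI helps prepare the evidence, and the PI chairs the board that shares in the recommendation. It does not extend to all oversight of the trial, given the IRB's role.

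The size is one of governance: no endpoint, estimate, power figure or analysis changes. It still needs correction before the Protocol is relied on, because a protection offered to critically ill subjects, some of them enrolled by surrogate consent, is not the one described. The conclusion assumes that attribution for the halting rule is the investigator classification in 5.4.3, the only one the Protocol provides.

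The word *continuous* in 5.5.2 is a separate and minor matter: it does not describe the meeting schedule in 5.4.4.

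**What to change.** Reconcile 5.4.1, 5.4.2 and 5.5.2 in one of two ways.

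- Preferred: state in 5.4.1 that the chair and all voting members are not investigators on this trial, and that the PI may present data in an open session but has no vote. The continuation recommendation in 5.4.2 would then involve a board that fits the description in 5.5.2.
- Otherwise: delete the word *independent* from 5.5.2, so that the Protocol does not claim a protection it lacks.

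In either case, replace *continuous* in 5.5.2 with the schedule in 5.4.4, including its provision for meetings as needed.

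The cost is small. If a listed member is already outside the study team, it is a change of chair and a few words. The Protocol does not say whether such a member exists; if none does, one outside chair has to be named, and any voting member who is an investigator on the trial gives up the vote. Recruitment, data collection and analysis are unaffected.

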**5.4.2 Data Safety Monitoring Plan**

Assuring patient safety is an essential component of this protocol. The study Principal Investigator has primary responsibility for the oversight of the data and safety monitoring. The study investigators will evaluate all adverse events. All subjects who have AEs, whether considered associated with the use of the study medication or not, must be monitored to determine the outcome. The clinical course of the AE will be followed up according to accepted standards of medical practice, even after the end of the period of observation, until a satisfactory explanation is found or the Principal Investigator considers it medically justifiable to terminate follow-up.

The study coordinators must view patient records for possible adverse events until 72 hours after the last dose of study drug. All untoward medical occurrences observed in subjects receiving the study drug will be recorded on the participants’ adverse event case report forms (CRF) by the study coordinator under the supervision of the principal investigator. The CRFs will then be reviewed for completeness and internal consistency. Subsequently, the CRFs will be recorded on an electronic password-guarded study database. In addition to internal safeguards built into a computerized system, external safeguards will be put in place to ensure that access to the computerized system and to the data is restricted to authorized personnel. Training conducted by qualified individuals on a continuing basis will be provided to individuals in the specific operations with regard to computerized systems that they are to perform during the course of the study.

The PI, will work with the reporting investigators to prepare a detailed written summary of serious, unexpected, and treatment related adverse events, and will compare, and contrast the event with prior events. The detailed written summary will be provided to the local DSMB and the IRB.

In addition, the DSMB Report addressed the following information will be submitted to the IRB at the time of continuing review annually or more often as required:

- A list of the research personnel who participated in the data and safety monitoring.
- The frequency of monitoring that took place during the renewal intervals and/or the dates that data and safety monitoring was conducted.
- A summary of cumulative data related to unanticipated problems (including adverse events) including a determination of causality and whether the risk to benefit assessment has changed.
- If appropriate, a summary of pertinent scientific literature reports, therapeutic developments, or results of related studies that may have an impact on the safety of study participants or the ethics of the research study.
- A summary of the outcome of reviews conducted to ensure subject privacy and research data confidentiality.
- Final conclusions regarding changes to the anticipated benefit-to-risk assessment of the study participation and final recommendations related to continuing, changing, or terminating the study.

Stopping Rule:

For safety reasons, we propose to discontinue this combined treatment if first 2 of the 10 subjects enrolled in the study experience any unexpected fatal or life-threatening events that can be attributed to the study drug, the study will be halted, until data review by investigators and the Data Safety Monitoring Board has rendered a final recommendation about study continuation.

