**5.4.6 Adverse Events Reporting Timeline**

Life-threatening or fatal unexpected adverse events associated with the use of the study drug or procedures must be reported to the DSMB and the IRB within 24 hours of discovery of the incident with subsequent follow-up submission of a detailed written report.

Serious (but not fatal or life-threatening) and unexpected adverse events associated with the use of the study drug or procedures must be reported to the DSMB and the IRB within 5 working days with subsequent follow-up submission of a detailed written report.

A summary report of the DSMB’s findings will be prepared and submitted to the regulatory agencies.

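### The protocol's only numeric halting rule (5.4.2) is worded so that it most naturally covers just the first two subjects, and it leaves unclear whether catheter or plasma-exchange events count

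*Protocol*

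**What the plan says.** The stopping rule closes Protocol 5.4.2. It opens with "we propose to discontinue this combined treatment", gives the condition that the "first 2 of the 10 subjects enrolled in the study experience any unexpected fatal or life-threatening events", and ends by limiting these to "events that can be attributed to the study drug, the study will be halted" until the investigators and the Data Safety Monitoring Board (DSMB) have reviewed the data. The sample size is 10 (2.4.1).

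No other section states a number of events that stops or pauses the trial. Section 5.4.3 provides for review of whether the study should continue, change or end. Section 5.4.4 provides for ongoing review by the principal investigator, team meetings every two weeks, and DSMB meetings as needed and at least six-monthly. Section 5.4.6 sets 24-hour reporting.

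On attribution, 5.4.6 is wider than the stopping rule for the same class of event: "Life-threatening or fatal unexpected adverse events associated with the use of the study drug or procedures must be reported". The protocol never defines the study drug. Section 5.4.3 says "Previous experience with rituximab has demonstrated common side effects that may occur during treatment" and then sets the causality scale: "Toxicity will be defined as an adverse event that is definitely, most likely, or possibly caused by the study drug". Section 5.4.2 has coordinators look for events "until 72 hours after the last dose of study drug", and 5.5.2 lists "Prior human experience with the study medication in similar conditions with an autoimmune hypothesis including rheumatoid arthritis and myositis" among the protections.

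**The concern.** Safety is a primary outcome (2.3.1), and this sentence is the only place where the protocol commits in advance to a count that halts treatment. A rule of this kind is applied as written, often under pressure, so it should have one meaning.

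**Count.** The sentence ties the number two to the order of enrolment. Followed that way, it lapses as a trigger after the second subject. One qualifying event in subject 3 and another in subject 4 would not invoke it, whether both or either of the first two is meant.

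**Attribution.** The rule would stop the whole combination but counts only events put down to an undefined study drug. The regimen includes a central venous catheter and five plasma exchanges (2.2.1). If staff take the study drug to be rituximab, an unexpected fatal event from the catheter or an exchange would be reported within 24 hours but would not count toward the halt. All five exchanges are scheduled on days 0 to 5. The first rituximab dose follows the last exchange on day 5.

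**Working it through.** The protocol states no operating characteristic for this rule, so there is no figure to reproduce. The check is what each possible reading would do.

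**Three readings of the sentence**

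- A: both of the first two enrolled subjects qualify.
- B: either of the first two enrolled subjects qualifies.
- C: any 2 of the 10 subjects qualify (the first two among the ten to have an event).

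A and B follow the printed order of words. C is less natural grammatically but is the likely intent.

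**Without an assumed event rate.** Input: 10 subjects (2.4.1). Assumption: enrolment order is unrelated to who has an event. Let k be the number of qualifying subjects among the 10.

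- A fires with probability C(8, k−2) / C(10, k).
- B fires with probability 1 − C(8, k) / C(10, k).
- C always fires when k is 2 or more.

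| k | A: both of first 2 | B: either of first 2 | C: any 2 of 10 |
|---|---|---|---|
| 2 | 1/45 = 2.2% | 1 − 28/45 = 17/45 = 37.8% | 100% |
| 3 | 8/120 = 6.7% | 1 − 56/120 = 53.3% | 100% |
| 4 | 28/210 = 13.3% | 1 − 70/210 = 66.7% | 100% |
| 5 | 56/252 = 22.2% | 1 − 56/252 = 77.8% | 100% |

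**With an assumed event rate.** The protocol gives no rate for unexpected, attributable, fatal or life-threatening events, so p below is an assumption shown over a range. Subjects are taken as independent. The last column is the chance that two or more of subjects 3 to 10 qualify, which neither A nor B can act on.

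- A: p²
- B: 1 − (1−p)²
- C: 1 − (1−p)¹⁰ − 10p(1−p)⁹
- Last column: 1 − (1−p)⁸ − 8p(1−p)⁷

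| p | A | B | C | 2 or more among subjects 3–10 |
|---|---|---|---|---|
| 0.05 | 0.0025 | 0.0975 | 0.0861 | 0.0572 |
| 0.10 | 0.0100 | 0.1900 | 0.2639 | 0.1869 |
| 0.20 | 0.0400 | 0.3600 | 0.6242 | 0.4967 |
| 0.30 | 0.0900 | 0.5100 | 0.8507 | 0.7447 |

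B is not uniformly laxer than C. At 5% it halts slightly more often, because one early event is enough. What A and B share is that they have nothing to say after subject 2.

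**Attribution, section by section.** Pointing to rituximab: the causality scale in 5.4.3 follows a remark on rituximab experience, 5.4.2 speaks of a last dose, and 5.5.2 cites prior use of the medication in rheumatoid arthritis and myositis. Pointing to the whole regimen: the rule's own object is the combined treatment, and 2.2.1 refers to plasma exchange and rituximab together as agents. Section 5.4.6 lists procedures beside the study drug, which suggests that the authors did not regard the one term as covering both. The text does not settle the matter.

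**The case against.** The strongest reply is that the sentence is simply broken English for any 2 of the 10, and that every investigator would read it so. A reader might otherwise infer that the rule definitely cannot act on eight of the ten subjects. The documents do not support that as a certainty, because reading C is available and is probably what was meant. What stands is that the printed words favour A or B and that nothing elsewhere supplies C.

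A reader might also infer that subjects 3 to 10 are unprotected. They are not. Sections 5.4.3, 5.4.4 and 5.4.6 give review and reporting for all ten, the DSMB can meet as needed, and termination is open to it. The rule itself yields a pause pending review. What is missing is the automatic trigger.

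On attribution, it is tempting to say that catheter and exchange events are excluded, or that 5.4.6 contradicts 5.4.2. Neither follows. Equating the study drug with rituximab is an inference, and it sits badly with the text: 5.4.3 defines an adverse event by receipt of the study drug, so nothing before day 5 would be one, whereas 2.4.2 counts new events from enrolment. A reporting duty may also properly be wider than a halting trigger. Moreover, the rule counts only unexpected events, a term that the protocol does not define, and 5.1.2 already lists bleeding, pneumothorax, clots and infection for the catheter, and hypotension, arrhythmia, seizures and transfusion reactions for the exchanges. If listed risks are taken as expected, widening the attribution would change little in practice. That limits the second point to a matter of clarity.

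**Conclusion.** The halting sentence is badly fixed and should be reworded. It is the only numeric safety trigger, and its printed form most naturally stops at the second subject. With exactly two qualifying subjects in random order, the chance of a halt is 2.2%, 37.8% or 100% depending only on how the sentence is read. At assumed rates of 5, 10, 20 and 30% the halt probabilities are 0.003, 0.01, 0.04 and 0.09 (both of the first two), 0.10, 0.19, 0.36 and 0.51 (either), and 0.09, 0.26, 0.62 and 0.85 (any two). The ordering figures rest on enrolment order being unrelated to events. The rate-based figures rest also on independence and on rates that the documents do not give. The higher rates may be well above what such narrowly defined events would show.

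The attribution wording is a secondary defect: it is unclear, not shown to be wrong, whether unexpected fatal or life-threatening catheter or exchange events count.

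**What to change.** Replace the stopping-rule sentence in 5.4.2 with one that halts enrolment and treatment for DSMB review once any 2 subjects treated to date, counted cumulatively, have had an unexpected fatal or life-threatening event attributed to the study drug or procedures, naming rituximab, plasma exchange and the central venous catheter. The sponsor and the DSMB should confirm the count of two. If a single event in either of the first two subjects was meant to stop the trial, that can be kept as an added early trigger. Use the same attribution wording in the causality sentences of 5.4.3.

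This is a short amendment with no change to data collection. If any 2 of 10 was always intended, it only writes that down. Against the reading as both of the first two, it raises the chance of a temporary pause (from 0.01 to 0.26 at an assumed 10% rate). Against the reading as either, it raises that chance at assumed rates of 10% and above and slightly lowers it at 5%.
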